## Abstract

**Background:**

Patient-reported outcomes (PROs) can be defined as any report of a patient’s health taken directly from the patient. Routine collection of PRO data has been shown to offer potential benefits to patient-doctor communication. Electronic forms of PRO measures (PROMs) could be more beneficial in comparison to traditional PROMs in obtaining PROs from patients. However, it is currently unclear whether the routine collection of electronic PRO data could result in better outcomes for patients undergoing laparoscopic cholecystectomy (LC).

**Objective:**

This study aims to explore the perspectives of patients and surgeons on the use of electronic PROMs. Based on prior research, technical skill and experience level of the surgeon, long-term quality of life, patient involvement in decision-making, communication skills of the surgeon, cleanliness of the ward environment, and standards of nursing care are identified to be the most important factors for the patients.

**Methods:**

This is a mixed methods prospective study that will collect both quantitative (survey) and qualitative (interview) data. The study has two components. The first involves the distribution of an electronic presurvey to patients who received elective LC within 48 hours of their surgery (n=80). This survey will explore the perspective of patients regarding the procedure, hospital experience, long-term outcomes, and the perceived value of using PROMs. These patients will then be followed up after 1 year and given another survey. The second component involves the distribution of the same survey and the completion of structured interviews with general surgeons (n=10). The survey will ascertain what PROs from the participants are most useful for the surgeons and the interviews will focus on how the surgeons view routine PRO collection. A convenience sampling approach will be used. Surveys will be distributed through Qualtrics and interviews will be completed on Microsoft Teams.

**Results:**

Data collection began on February 14, 2023. As of February 12, 2024, 71 of 80 recruited patients have been given the presurvey. The follow-up with the patients and the general surgeon components of the study have not begun. The expected completion date of this study is in April 2025.

**Conclusions:**

Overall, this study will investigate the potential of electronic PRO collection to offer value for patients and general surgeons. This approach will ensure that patient care is investigated in a multifaceted way, offering patient-centric guidance to surgeons in their approach to care.

**International Registered Report Identifier (IRRID):**

DERR1-10.2196/57344

## Introduction

### Patient-Reported Outcomes

Patient-reported outcomes (PROs) can be defined as any report of a patient’s health outcome taken directly from the patient [1]. PROs are normally investigated through the use of standardized patient-reported outcome measures (PROMs), which are typically self-completed questionnaires that measure patient quality of life, symptom burden, functional status, health-related quality of life, and personal care experience [2,3]. The investigation of PROs allows for the generation of a health care system that is truly patient-centered [4]. Patient-centered health care has already proven to improve health status and the efficiency at which care is delivered [5]. Thus, it would be beneficial to understand the measures that could be taken to improve PROs after the completion of surgical procedures such as laparoscopic cystectomy (LC). PROs are particularly relevant to LCs since patients undergo this operation to relieve their pain; thus, measuring PROs after the procedure is crucial [6].

A systematic review demonstrated that most studies evaluating the effects of LC did not use an electronic method of measuring PROs, despite advances in technology [7]. Another systematic review concluded that there is limited literature regarding the use of electronic PRO systems in surgery, and the authors proposed that future research should explore the challenges associated with using such systems [8]. A more recent systematic review found that the integration of electronic PROM systems through the use of mobile apps has the potential to improve patient outcomes and the efficiency of hospital resources [9].

Han et al [6] demonstrated that LC results improved PROs regarding pain, quality of life, and the relief of gastrointestinal symptoms. Several factors significantly influence PROs after LC. For instance, a 2019 study in Singapore found that the technical skill and experience level of the surgeon, long-term quality of life, patient involvement in decision-making, communication skills of the surgeon, cleanliness of the ward environment, and standards of nursing care were crucial factors that influence PROs [10]. Conversely, factors such as hospitalization leave duration, length of hospital stay, the opinion of the patient’s family about the hospital, and scar cosmesis were factors with relatively less importance on PROs [10].

### Patient-Reported Experiences

Patient-reported experience measures (PREMs) are tools used to report on a patient’s process of care (eg, communication and timeliness of care) rather than on the outcomes specifically [2,11]. PREMs are a useful predictor for overall patient satisfaction [12]. As a result, PREMs will also be used in this study to evaluate the hospital experience of the patient.

### Routine Collection of PROs in Other Specialties

The implementation of routine PRO collection has been shown to be beneficial and feasible in various health care fields such as oncology, cardiology, and integrative medicine [13-16]. However, the integration of routine electronic PRO collection in oncology is currently limited due to inadequate information technology infrastructures, time, and difficulty in using electronic devices [17]. In the field of ophthalmology, one pilot study indicated that ophthalmologists recognized the powerful potential benefits of electronic PROs for patient-doctor communication [18]. Furthermore, an observational study [19] investigated whether passive collection of behavioral data could be associated with PROs using patients’ smartphone sensors and activity data, demonstrating that patients with lower activity levels tended to have poorer PRO scores. While the passive monitoring of PROs is beyond the scope of this project, this previous work highlights the immense potential benefits that routine PRO monitoring could have for LC and other general patients.

In the field of surgery, systematic reviews have indicated that routine PRO collection has benefits in relation to colorectal and orthopedic surgical specialties [20,21]. One quality improvement study also indicated that routine PRO collection was a critical factor in improving thoracic surgery care [22]. Although the logistical implication of routine collection remains the most challenging factor, the advancement of technology could assist in solving this issue. Thus, electronic PROMs could be useful for patients undergoing LC, which will be explored in this study.

### Routine Collection of PROs

The evidence that PROs can be useful as a feedback tool in surgery to improve patient outcomes is currently limited. One study indicated that there is currently only weak evidence that PROs provide any benefit to patient outcomes when used as a feedback tool [23]. Furthermore, more qualitative research is needed to investigate the practical issues that could arise with routine PRO collection [23,24]. However, another systematic review exploring routine PRO monitoring during cancer care demonstrated significantly improved health-related quality of life among patients [25]. These conflicts demonstrate a lack of clear consensus regarding the routine collection of PROs. Thus, this study will investigate the perspective of surgeons on PRO collection. These data could elucidate the type of feedback that is most relevant for surgeons to improve care. In addition, qualitative interviews will be conducted with the surgeons to obtain insight into the potential benefits and barriers of routine PRO collection.

The use of routine PRO collection specifically in relation to LC is currently very limited. One feasibility study investigating the use of electronic PROMs indicated that the collection of such measures could be a convenient process for patients that would be beneficial in evaluating quality-of-life trends for physicians [26]. Authors have also proposed the need for future research with more robust methodologies such as randomized controlled trials exploring this area. Using electronic PROMs has been indicated to help resolve the logistical and cost issues associated with PROM collection [13,26].

### Study Objectives

This study aims to explore the perspectives of patients and surgeons on the use of electronic PROMs. These perspectives will be investigated through the distribution of surveys to both groups and via the completion of interviews with the general surgeons.

The specific objectives of the study include (1) understanding the acceptability and perceived value of electronic PROs from the perspective of both patients undergoing LC and general surgeons and (2) determining the feasibility of following up with patients regarding their PROs using email correspondence.

## Methods

### Study Design and Overview

This is a mixed methods prospective study that will collect both qualitative and quantitative data. The study will involve two components. The first is the distribution of a survey to patients who have completed an elective LC. The second smaller component is the distribution of the same survey to consultant surgeons in addition to the completion of structured qualitative interviews with the same surgeons. This is an observational study and will have no influence on the care of patients.

### Component 1: Patient Survey

#### Patient Participants

The subjects will include all patients who completed elective LCs from Cork University Hospital and Mercy University Hospital, both in Cork, Ireland. Patients undergoing LC were chosen for this study owing to the high number of LCs completed in these hospitals. This makes the study more feasible and realistic to complete.

#### Inclusion Criteria

Patients must be >18 years old and have completed an elective LC. Patients must have the capacity to access the Qualtrics survey through their smartphone and have completed the LC within 48 hours of distribution of the first survey. For the sake of feasibility, any indication for the elective LC will be eligible for recruitment in this study to ensure an adequate sample size.

#### Exclusion Criteria

Patients who cannot read, are pregnant, have a mental disability, have dementia, or do not speak English will be excluded. Additionally, patients who are sedated, ventilated, or intubated will be excluded as they will not be capable of offering informed consent.

#### Sample Size

This study will aim to recruit 80 patients. This sample size was chosen for the sake of feasibility. Due to time constraints, with 10 months of allocated time for data collection and 2 participating hospitals collaborating on the project, it would not be feasible to collect more data.

Power calculation was considered for determining the sample size. However, power calculation requires an estimation of the proportion of the event of interest [27]. For this study, it would be unrealistic to estimate the number of elective LCs that are completed in Ireland, as these data are not readily available. Consequently, it was decided to estimate the sample size primarily based on feasibility rather than power.

#### Recruitment of Patient Participants

Participants will be recruited using a nonprobability convenience sampling approach. The patients undergoing elective LCs will be viewed from the daily theater list and through communication with the operating surgical team*.* Participating patients will be identified as eligible by surgeons from Cork University Hospital who are collaborating in this study. The participant information sheet and consent form will be integrated into the beginning of the Qualtrics survey.

After completion of the presurvey, the participants will be sent a link for the postsurvey 12 months later through email. The recruitment and data collection flow for patients is presented in Multimedia Appendix 1.

#### Patient Participant Survey

The survey will be based on the PROM questionnaire, which measures the effect of different factors on the PROs [10]. The following factors will be measured using the PROM survey: (1) age, sex, education level, marital status, employment status, ethnicity, smoking, and exercise frequency; (2) procedure perception; (3) hospital experience perception (PREMs); and (4) perception of longer-term consequences.

In addition, the acceptability and perceived value of the PROMs will be assessed with a survey from Stover et al [28].

The presurvey will be administered electronically by email using Qualtrics to patients who have completed an elective LC within the past 48 hours. These patients will then be followed up after 1 year and the survey will be administered again (Multimedia Appendix 2).

#### Other Data Collection Tools Considered

Other PRO surveys such as the Gastrointestinal Quality of Life Index survey and visual analog pain scores were also considered [29,30]. However, we ultimately determined to not use these tools in this study, as they only measure the PROs directly rather than determining what PROs and experiences patients find most important to them. Including a combination of these surveys could have been optimal, but it would have resulted in an overly long survey and potentially poor participant completion rates.

### Component 2: Surgeon Survey and Interview

#### Surgeon Population

Ten general surgeons will be recruited from Cork University Hospital and Mercy University Hospital. This sample size was chosen based on the feasibility within these hospital settings.

#### Inclusion Criteria

Only general surgeons will be included, as they represent the group that would be most knowledgeable about LC, which is the surgery that the study is based around. The surgeons must have been registrars, specialist registrars, or consultants for at least 1 year in a general surgery team. They must be currently employed within Cork University Hospital or Mercy University Hospital.

#### Exclusion Criteria

The surgeons involved in the creation of this study will be excluded from participation.

#### Recruitment of Surgeon Participants

The participants will be recruited using a nonprobability consecutive sampling approach. They will be briefed on the study using an information sheet and given a consent form for the interview.

#### Interview

All the surgeon participants (n=10) will also be interviewed using an interview guide adapted from the PROFILE trial [24]. The interviews will take place online using Microsoft Teams. The interviews will explore the following factors: (1) background of PRO use by the surgeon, (2) attitude of the general surgeon toward PRO use, (3) perception of the surgeons regarding the impact that PROs can have on clinical practice, and (4) perception of the surgeons regarding practical issues regarding PRO collection (Multimedia Appendix 3 and Multimedia Appendix 4).

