#### Data Analysis

SPSS v28.0.1.1 (IBM Corp) will be used to complete the data analysis for the patient surveys. The 4-point Likert-scale questions will be tallied into two categories of either “more important” or “less important.” Mean scores will be used to determine the most important and least important factors. Univariate analysis with χ^2^ tests will then be used to determine if any demographic relations exist between what PROs participants find to be more or less important. Additionally, the Wilcoxon ranked sign test and 2-tailed ANOVA will be used to compare the differences between the patients’ answers in their first and second survey responses.

Data from the survey for the surgeons will also be analyzed with SPSS. Mean scores will be tabulated for the general surgeons’ responses to the survey. For the general surgeons’ interviews, the results will be transcribed verbatim and analyzed with thematic synthesis [24]. The qualitative data will explain the overall view that surgeons have regarding PRO collection and the quantitative data will be analyzed in conjunction to illustrate the specific PROs that the surgeons view as important. The patient and surgeon data will also be integrated by comparing the views that both stakeholders have as indicated in the PROM surveys.

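### Objective 1 asks for surgeons' views on electronic PROs, but the surgeon interview and survey, as described, do not target the electronic mode, so those views may not be elicited

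*Protocol article*

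**What the plan says.** Study Objectives gives the overall aim: "This study aims to explore the perspectives of patients and surgeons on the use of electronic PROMs". Its first specific objective is "understanding the acceptability and perceived value of electronic PROs from the perspective of both patients undergoing LC and general surgeons". The same section names the means: surveys to both groups, and for surgeons also "via the completion of interviews with the general surgeons".

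The Interview section lists four topics. The first is the surgeon's own history with PROs, the second and third are "2) attitude of the general surgeon toward PRO use, (3) perception of the surgeons regarding the impact that PROs can have on clinical practice", and the fourth is practical issues in collecting PROs. The section refers to appendices for the detail. The Abstract (Methods) says that "the interviews will focus on how the surgeons view routine PRO collection". The Introduction, under Routine Collection of PROs, likewise gives the purpose of the interviews as the benefits and barriers of routine collection. Data Analysis says: "The qualitative data will explain the overall view that surgeons have regarding PRO collection".

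The Surgeon Survey section describes a modified questionnaire restricted to three domains: the procedure, the hospital, and longer-term consequences. The instrument for acceptability and perceived value appears only under Patient Participant Survey. Yet the Abstract (Methods) and Study Design and Overview both say that surgeons receive the survey given to patients.

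The conclusions of the Abstract and of the Discussion say that the study will examine the value of electronic PRO collection for patients and for general surgeons.

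**The concern.** The surgeon part of the study is defined in two ways. The aim, Objective 1 and the conclusions concern the electronic mode. The interview topics, the interview's stated focus and the analysis aim concern PRO use, or routine PRO collection, whatever the mode.

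These are different questions. A surgeon may value PROs and doubt electronic collection, or accept the electronic mode and see little use in PROs. An interview that asks only about PROs in general need not bring out either view. If the electronic mode is not raised, the study has no planned surgeon data on that part of Objective 1, and its statement on electronic collection for surgeons would rest on whatever surgeons happened to volunteer.

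**Working it through.** No arithmetic beyond a count applies, and no figure in the plan is disputed. The check follows Objective 1 through each surgeon instrument to the analysis and the conclusion.

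| Step | Place in the protocol article | Object of study for surgeons |
|---|---|---|
| Aim and Objective 1 | Study Objectives | Electronic PROMs/PROs: acceptability and perceived value |
| Interview focus | Abstract (Methods); Introduction, Routine Collection of PROs | Routine PRO collection |
| Interview topics | Interview | PRO background, attitude, impact, practical issues |
| Survey content | Surgeon Survey | Importance of procedure, hospital and longer-term factors |
| Interview analysis | Data Analysis | Overall view on PRO collection |
| Conclusion | Abstract and Discussion, Conclusions | Value of electronic PRO collection |

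1. **Interview.** Of 4 listed topics, 0 name electronic collection. Topics 2 and 3 come closest to acceptability and value, but for PROs in general. Topic 4 could reach the electronic mode, but it is about practical issues.

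2. **Routine is not a synonym for electronic here.** The Introduction's section on other specialties speaks both of routine PRO collection and of routine electronic PRO collection, so the article treats the electronic mode as a further attribute.

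3. **Survey.** Of 3 domains, 0 measure acceptability or perceived value of PROs in any mode. This does not depend on whether the word electronic appears: the three domains concern which patient feedback matters to the surgeon.

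4. **Conflict over the survey.** If surgeons did receive the patients' survey, they would receive its acceptability items. The Surgeon Survey section is the specific description, and it confines the modified version to three domains. Both descriptions cannot be right.

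5. **Result.** The objective and the conclusion name the electronic mode, and nothing stated between them does. All 10 surgeons could complete both instruments as described without being asked about the electronic part of Objective 1.

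**The case against.** The strongest reply is that the interview guide is not shown. An article normally condenses a guide to headings, and the guide may contain prompts on electronic delivery. This stands, and it makes the point conditional. It does not remove it, because the focus, topics and analysis aim that the article does state all agree with each other and differ from the objective.

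Second, the article often drops the word electronic. Patient Participant Survey describes the patients' acceptability instrument as being about PROMs, while the Discussion (Study Significance and Strengths) describes that assessment as being about electronic surveys. So a missing word in a heading does not prove a missing construct. This also stands for the interview topics. It does not help the surgeon survey, which as described has no acceptability or perceived-value items at all.

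Third, topic 4 may partly reach the electronic mode, since the Introduction links the logistics of routine collection to technology. That is fair, but practical issues cover at most part of acceptability and perceived value.

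A reader might go further and infer that general views will be reported as views on electronic collection, or that surgeons with opposite views on the electronic mode will be coded alike. The documents support neither. Data Analysis plans verbatim transcripts and thematic synthesis and states no fixed coding frame, so a view that is voiced can form its own theme. It also describes the interview output only as a view on PRO collection. The supported risk is narrower: the view may never be elicited.

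A reader might also fault the plan for leaving out infrastructure barriers to electronic systems. Limitations already says that the study does not address these, so this is a disclosed limit of scope.

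**Conclusion.** The point holds in a limited form. As described, no surgeon instrument targets the electronic part of Objective 1 (0 of 4 interview topics, 0 of 3 survey domains), and the article describes the surgeon survey in two incompatible ways. Subject to the interview guide, the 10 surgeons' views on the electronic mode may not be elicited, and the planned statement on its value for surgeons could not then be supported.

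This rests on two assumptions: that the topic list fairly represents the guide, and that the three-domain description of the surgeon survey is the operative one. If the guide does ask about acceptability and value of electronic collection, or if surgeons do receive the acceptability items, what remains is to align the wording. The patient part of Objective 1 is not affected.

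**What to change.** - **Interview or survey.** Before the interviews planned for March and April 2025, add the acceptability and perceived value of electronic collection as an explicit topic in the Interview section and in the guide. Alternatively, include the patients' acceptability items in the surgeon survey.
- **Analysis.** In Data Analysis, state that themes about the electronic mode will be reported separately from themes about PROs in general, and base the conclusion about electronic collection for surgeons on the former only.
- **Survey description.** Reconcile the Abstract (Methods) and Study Design and Overview with the Surgeon Survey section, so that it is clear whether surgeons receive the acceptability items.
- **If no instrument is changed.** Reword the surgeon part of Objective 1, and the conclusions in the Abstract and Discussion, to routine PRO collection in general. This is also the remedy if the interviews have already been held without such a topic.

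Infrastructure barriers need not be added. The cost is a revised guide and a slightly longer interview or survey for 10 surgeons. The surgeon component had not begun when the article was written, so a change at that stage would lose no data.
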